### 2.6.2 Secondary endpoints

1. - IPAQ: Total and subtotal domain specific scores (work, leisure-time, transport,

domestic & garden [MET-min/week] and sitting time [min/week])

1. - SF-36: Total and subtotal domain specific scores (9 domains)
2. - VAS: Scores of perceived work and leisure-time physical exertion and effort
3. - Borg scale: Values of rated physical exertion at work (midday and evening)
4. - Results of the 20 meter shuttle run: predicted VO2max [METs]
5. - Results of the SenseWear Mini armband in recreation: activity and energy scores

as listed above

### 2.6.3 Statistical analysis

Statistical analyses will be done using the software R (version 2.15.1) and IBM SPSS Statistics (version 19.0). Statistical significance will be acquired if a p value of less than 0.05 is attained.

Data will be presented by descriptive statistics within occupational groups. Cross tables are reported as counts and percentages. Ordinal variables are reported as median and Interquartile range (IQR). Metric variables are reported as mean and standard deviation (SD).

To evaluate primary endpoints, linear regressions will be performed. Independent variable is “occupational group”, dependent variables are “average daily active energy expenditure”, “average daily physical activity duration” and “average daily number of steps”. Optionally, personal and job related factors can be included in the regression analyses as covariates. If appropriate, data will be log-transformed. Regression results will be presented as differences of means between “occupational categories” with corresponding 95% confidence intervals (C.I.) and p-values. In case of logarithmic distributed data, geometric mean ratios will be presented.

To evaluate secondary endpoints, linear regressions will be conducted. In case of ordinal variables, non-parametric methods will be applied.

Furthermore, the mean and individual time courses of physical activity periods will be plotted for all primary and secondary variables.

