## 2.2 Selection of study participants

### 2.2.1 Recruitment

In this study, it is intended to recruit 300 subjects from different occupational groups with low, middle and high occupational activity, which are defined in a later section (see chapter 2.3.2). Based on this classification, companies will be selected. In each occupational group, 100 participants will be enrolled. Furthermore, homogeneity of age and gender within each group will be aimed at recruiting.

First, we will contact the management of potential enterprises in order to present our project. If they are interested in collaboration, we will ask for a list of employees, who will then be addressed by a member of our research team. In a further step, individuals will be informed and asked for study participation by phone or by mail. Furthermore, it is planned to distribute study flyers in the companies, so that interested employees have the opportunity to contact us directly. In both situations, the recruitment and information process will be done externally. Thus, negative impact of the employer can be avoided and the selection of study participants will occur randomly. However, the employer’s agreement is essential for the conduction of the study.

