### Primary endpoints

Primary endpoints will include the following measurements of the SenseWear Mini armband during working time:

1. - Average daily active energy expenditure [cal]
2. - Average daily physical activity duration at different intensities [min]

(Low (<3.0 METs), middle (3.0-6.0 METs), high (6.0-9.0 METs) and very high (>9.0 METs))

1. - Average daily number of steps
2. - Graphs with plotted distribution of physical activity periods

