### 2.6.4 Sample-size calculation

Since “average daily active energy expenditure” measured by the SenseWear Mini armband represents a valid and reliable parameter, it is considered to be the most important primary endpoint of the present investigation. For this reason, only this variable is subject to a power calculation. In a previous study, the SD of “average daily active energy expenditure” during a normal work shift was found to be 730 kcal . The expected mean difference between the three occupational groups will be around 500 kcal. Assuming a sample size of 100 subjects in each occupational group, there is a power of >90% to detect a mean difference of 500 kcal between any of these groups. This calculation is based on the assumption of a within group SD of 730 kcal and on a two-sided significance level of 5%.

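### Several co-primary activity variables are compared between three groups at a flat 0.05, and the ranking of energy expenditure as most important never reaches the analysis

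*Protocol*

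**What the plan says.** Section 2.6.1 opens its list with "Primary endpoints will include the following measurements of the SenseWear Mini armband during working time". The list holds active energy expenditure, activity duration in four MET bands, number of steps, and plots of activity periods. Leaving out the plots, that is six numeric variables. Section 2.6.3 names three dependent variables for the regressions, with duration as a single item, so the count is either three or six.

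Section 2.6.3 reports differences of means between occupational groups with confidence intervals and p-values, and sets one threshold: "Statistical significance will be acquired if a p value of less than 0.05 is attained". It gives no overall test as a first step, no order of testing and no adjustment.

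Section 2.6.4 says of energy expenditure that "it is considered to be the most important primary endpoint of the present investigation", and for that reason powers only this variable. Its power statement, made at a two-sided 5% level, is that "there is a power of >90% to detect a mean difference of 500 kcal between any of these groups".

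**The concern.** Three groups give three pairwise comparisons per variable, and each may be declared significant at 0.05. The protocol does not say which result carries the primary conclusion. The one sentence that ranks the endpoints sits in the sample-size section and has no consequence in the analysis section. A significant difference in any band, or in steps, between any two groups could therefore be reported as a positive primary result, with a chance of a false claim above the nominal 5%. Section 1.4 expects the results to inform return-to-work recommendations, so a reader should be able to tell which differences are confirmed.

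**Working it through.** **Inputs from the protocol.** 100 participants per group in three groups (2.2.1, 2.6.4); difference 500 kcal, within-group SD 730 kcal, two-sided 5% (2.6.4); threshold 0.05 (2.6.3).

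**Input not in the protocol.** The correlation between primary variables. I assume one common value and vary it from 0 to 0.9.

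**1. The stated power.** The standard error of a difference is 730 × √(2/100) = 103.24 kcal. The standardised difference is 500/103.24 = 4.843. Power ≈ Φ(4.843 − 1.960) = Φ(2.883) = 99.8%. The stated figure of more than 90% for one unadjusted pair is correct and conservative.

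**2. Energy expenditure alone, three unadjusted pairs.** If the three means are equal, the chance that at least one pair has p < 0.05 is the upper tail of the studentized range for 3 groups and 297 degrees of freedom at √2 × t(0.975; 297). This is 12.2%. It is below the 1 − 0.95³ = 14.3% for independent tests because the pairs share groups.

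**3. The whole primary set, no variable differing between any groups, all three pairs tested.** Simulation with 200,000 runs:

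| Assumed correlation | Three variables (9 tests) | Six variables (18 tests) |
|---|---|---|
| 0 | 32% | 54% |
| 0.5 | 28% | 44% |
| 0.7 | 25% | 35% |
| 0.9 | 19% | 24% |

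Treating 18 tests as independent would give 1 − 0.95¹⁸ = 60%, which is too high for the reason given in step 2.

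**4. A less extreme case.** Suppose the high-activity group truly differs on every variable, but the low and middle groups do not differ on any. Only one pair per variable can then yield a false claim. For six variables the chance of at least one is 27%, 21%, 16% and 11% at correlations 0, 0.5, 0.7 and 0.9. For three variables it is 14%, 13%, 11% and 8%. For energy expenditure alone it is 5%.

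**5. Power when the pairs are tested only after a significant overall test.** The overall test is the 2-df F test at 5% with noncentrality 100 × Σ(μᵢ − μ̄)²/730².
- Means 0, 500, 1000 kcal (500 kcal between neighbouring groups): noncentrality 93.8; the overall test is practically certain to be significant, and power for a 500 kcal pair stays at 99.8%.
- Two groups equal, the third 500 kcal away: noncentrality 31.3, overall power 99.9%, gated pair power 99.8%.
- Least favourable case, third group midway between two groups 500 kcal apart: noncentrality 23.5, overall power 99.4%, gated pair power 99.4%.

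**6. Bonferroni over 18 tests, for comparison.** At 0.05/18 = 0.00278 the critical value is 2.991. At 500 kcal, power is Φ(4.843 − 2.991) = 96.8%. At 300 kcal the standardised difference is 300/103.24 = 2.906, and power falls from Φ(2.906 − 1.960) = 82.8% to Φ(2.906 − 2.991) = 46.6%.

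**The case against.** **Multiplicity is usually left to the SAP.** Only the protocol is at hand, and section 2.6.3 does not say that p-values will be unadjusted; adjusted p-values could also be compared with 0.05. This has some force. However, the protocol does more than stay silent. It states the threshold, claims power for any pair at 5%, and ranks the endpoints without using the ranking in the tests. An SAP would have to supply a structure that the protocol's own analysis section does not contain.

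**The groups are bound to differ.** Section 2.3.2 forms them as low, middle and high occupational activity, and section 1.3 expects heavy workers to expend more energy. This stands: no difference on any variable is unlikely, so the figures in step 3 are a ceiling. Step 4 shows that the excess shrinks but persists across the primary set when one group truly differs.

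**The count of tests is a reading.** Section 2.6.3 can be read as three variables, and section 2.6.1 supports six. All-pairs testing is suggested by section 2.6.4 but not spelled out in 2.6.3. The bands divide the same working time, so a common correlation is only a rough model. All of this is why ranges are given.

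**The study is cross-sectional and largely descriptive.** Strict familywise control is partly a matter of judgement here, and each single test keeps its own 5% level. Even so, a protocol that names primary endpoints, a power claim and a significance rule should say which comparison is confirmatory.

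**Two stronger readings are not supported.** A reader might infer that the study has about an even chance of a false primary claim. That needs no true difference on any variable, six variables, all pairs and low correlation together. A reader might also infer that correcting for all 18 tests costs almost no power. That can be shown only for energy expenditure at 500 kcal. At 300 kcal the cost is large, and the protocol gives no SD or effect for the other variables.

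**Conclusion.** The concern holds. The protocol tests three or six co-primary variables between three groups at a flat 0.05, and leaves its own ranking of energy expenditure unused. The firmest figure is about 12% familywise error for the three energy-expenditure pairs if that variable does not differ; it needs no assumed correlation between variables. For the whole primary set the worst case is about 19–32% with three variables or 24–54% with six. It rests on no true differences, all pairs tested, and an assumed common correlation between 0.9 and 0. The actual error is lower where differences are real. The sample size and the power claim are not in doubt.

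**What to change.** In 2.6.1, name average daily active energy expenditure during working time as the single confirmatory primary endpoint, as 2.6.4 already suggests. In 2.6.3, test the overall 2-df effect of occupational group on it at 5%, and test the three pairs at 5% each only if the overall test is significant. With three groups this is a closed procedure and holds the familywise error for that endpoint at 5%.

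Then either test the protocol's own remaining variables (steps and the existing duration bands) in an order fixed in advance, or report them with 95% confidence intervals as supportive. If they are tested in order, state the condition for moving on. Moving on only when all three energy-expenditure pairs are significant, with the same rule at each later step, keeps 5% control over the pairwise claims. With 500 kcal between neighbouring groups, the chance that both neighbouring pairs are significant is 99.6%. Moving on after the overall test alone does not give that control.

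The cost is wording in two sections and no extra participants. Power for a 500 kcal pair stays at about 99.8% (99.4% in the least favourable arrangement of means). The small downside is that steps and the duration bands lose stand-alone confirmatory status, although duration at different intensities is part of the stated primary aim in 1.2. They would still be estimated and reported.

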### 2.6.4 Sample-size calculation

Since “average daily active energy expenditure” measured by the SenseWear Mini armband represents a valid and reliable parameter, it is considered to be the most important primary endpoint of the present investigation. For this reason, only this variable is subject to a power calculation. In a previous study, the SD of “average daily active energy expenditure” during a normal work shift was found to be 730 kcal . The expected mean difference between the three occupational groups will be around 500 kcal. Assuming a sample size of 100 subjects in each occupational group, there is a power of >90% to detect a mean difference of 500 kcal between any of these groups. This calculation is based on the assumption of a within group SD of 730 kcal and on a two-sided significance level of 5%.

## 2.7 Duties of the investigator

This study will be conducted in compliance with the approved research protocol. In case of any considerable deviations from study protocol, the investigator will send an amendment for further approval to the corresponding Ethical Committee.

Furthermore, the investigator declares that the insurance coverage for total study length will be assured before enrolling subjects into the present investigation. However, study participants will not receive financial compensation for their participation.

## 2.8 Ethical consideration

### 2.8.1 Informed consent of study participants

Prior to study entry, participants will be given an information sheet about the aim, procedures and potential risks of the study. Only after signing the informed consent form, subjects will be submitted to any study procedures. The documents used in this study will be submitted with the protocol to the Ethical Committee for approval.

### 2.8.2 Risks and benefits for study participants

In general, the present investigations are low-risk. However, by wearing the SenseWear Mini armband, allergic skin irritations may occur at the point of contact. Moreover, sleep quality might be slightly impaired during the measurement period of one week, since the armband will be continuously worn, including while sleeping. In addition, the performance of the 20 meter shuttle run representing a maximal exercise test, could lead to exertional dyspnea and a decrease of oxygen saturation that require test termination. Other risks of this study are related to privacy issues. Therefore, subjects will be anonymized and data will be entered only into password-protected computers at the University Hospital. Furthermore, measurements are intended to be conducted at the individual’s workstation in order to minimize loss of working time.

On the other hand, participants may profit from data about daily energy expenditure, number of steps and physical activity duration at different intensities. Since these parameters will be assessed during work and recreation, subjects will receive detailed information about physical work requirements as well as active leisure-time behaviour. Furthermore, results on exercise capacity will be provided. The findings of this study, concerning performance criteria of different job categories, may also be beneficial for other individuals, who need to be reintegrated into daily work after an accident or illness.

## 2.9 Publication and authorship

It is planned to publish the present study in a work, health and activity related journal, as for example ‘Journal of Occupational Rehabilitation’, ‘Journal of Occupational and Environmental Medicine’, ‘Occupational and Environmental Health’, ‘Medicine and Science in Sports and Exercise‘ or ‘International Journal of Sports Medicine’.

A first publication will focus on the characterization of professions regarding physical activity profiles and performance criteria. These results could be implemented in the areas of prevention and occupational rehabilitation in order to evaluate individual’s job qualification as well as work ability. In a second study, the relationship between exercise capacity and work and non-work related physical activity will be investigated. These results might be valuable to assess the interaction between work load and work capacity.

The authors of the publication will be determined by [name] (first author) and [name] (principle investigator) prior to submission based on their contributions made during the project. Participants without significant involvement in all stages of the project will be listed in the Acknowledgements. Furthermore, a mention in the protocol is not necessarily equated to authorship.

